## Abstract

**Background:**

Hypertension is a leading modifiable risk factor for cardiovascular disease and premature death among adults. Up to 18% of individuals with hypertension have resistant hypertension (rHTN), which substantially increases the risk of adverse clinical outcomes. Endogenous hypercortisolism can result in rHTN through multiple mechanisms.

**Objectives:**

MOMENTUM (NCT06829537) is the first large, observational, multicenter study examining the prevalence of endogenous hypercortisolism among adults with rHTN in the United States.

**Methods:**

Target enrollment is approximately 1,000 participants. To be eligible, adults aged ≥18 years must have rHTN, defined using the American Heart Association criteria (systolic blood pressure ≥130 mm Hg despite ≥3 antihypertensive medications of different classes at maximally tolerated doses, including a diuretic, or ≥4 medications from different classes regardless of systolic blood pressure). Endogenous hypercortisolism is defined as cortisol level >1.8 μg/dL on the 1-mg overnight dexamethasone suppression test with adequate dexamethasone (≥140 ng/dL). The primary endpoint is endogenous hypercortisolism prevalence.

**Conclusions:**

MOMENTUM will provide new insight into endogenous hypercortisolism in patients with resistant hypertension.

Hypertension is a leading modifiable risk factor for cardiovascular disease, stroke, disability, and premature death, affecting nearly half of adults in the United States.^1^, ^2^, ^3^ In 2019, annual health care costs associated with hypertension care in the United States were $2,759 per person, totaling $219 billion annually nationwide.^4^ Lifestyle modifications in combination with blood pressure–lowering medications, the primary means of controlling hypertension, are effective in many patients.^3^ However, a significant percentage of individuals, estimated at 9% to 18%, exceed the American Heart Association (AHA) systolic blood pressure (SBP) target of ≥130 mm Hg despite using ≥3 different antihypertensive agents (including a diuretic) or require ≥4 medications from different classes to achieve control, a clinical condition defined as resistant hypertension (rHTN).^2^^,^^3^^,^^5^ Adults with rHTN have an increased risk of ischemic heart disease, myocardial infarction, transient ischemic attack, stroke, end-stage renal disease, and premature mortality,^2^^,^^3^^,^^6^^,^^7^ as well as greater health care resource utilization,^6^^,^^8^ compared with those with controlled hypertension. The high clinical and economic burden associated with rHTN underscores a need for improved diagnosis and management of this condition.^8^, ^9^, ^10^

Difficult-to-control hypertension despite lifestyle changes and optimized medical management may involve secondary contributing factors.^3^ Primary aldosteronism is one common—albeit widely underdiagnosed—cause of rHTN. Endogenous hypercortisolism is another known contributing rHTN cause which remains largely unstudied.^3^^,^^11^^,^^12^ Endogenous hypercortisolism is a state of chronic cortisol excess that can arise from several abnormalities, including production of excess adrenocorticotropic hormone (ACTH) from a pituitary or ectopic tumor or the autonomous secretion of cortisol in the adrenal gland.^13^^,^^14^ In individuals without the classic physical manifestations often associated with overt Cushing disease (an extreme form of hypercortisolism usually with a pituitary etiology), endogenous hypercortisolism presenting as hypertension often has an adrenal origin.^14^

Epidemiological studies in individuals with type 2 diabetes (T2D) and other comorbidities reveal an association between endogenous hypercortisolism and hypertension, including rHTN. The CATALYST study, the largest observational study of endogenous hypercortisolism prevalence, screened over 1,000 U.S. adults with difficult-to-control T2D and found that approximately one-quarter of these individuals had endogenous hypercortisolism. Furthermore, a significantly higher proportion of individuals with endogenous hypercortisolism had hypertension (89% vs 79%; *P* < 0.001) and were taking ≥3 antihypertensive medications (38% vs 23%; *P* < 0.001) compared to those without hypercortisolism.^15^ A prior meta-analysis of 6 studies in individuals with T2D reported that the presence of hypertension was associated with a 2-fold increase in the likelihood of endogenous hypercortisolism.^16^

The prevalence of endogenous hypercortisolism among adults with rHTN in the United States remains unknown. The standard overnight dexamethasone suppression test (DST)—involving a 1-mg dose of dexamethasone the night before a morning blood draw—is the most sensitive test for detecting adrenal hypercortisolism, the form most likely found in individuals presenting with T2D as their initial medical complaint.^13^^,^^17^^,^^18^ Despite the relative simplicity of this test, screening for endogenous hypercortisolism is uncommon due to the perceived rarity of the condition and the perception of screening challenges.^19^^,^^20^ The CATALYST study showed that by excluding common causes of false-positive results, the standard overnight DST can identify individuals with endogenous hypercortisolism, thus facilitating medical management.^15^^,^^21^ Furthermore, hypercortisolism was even more likely among participants on multiple antihypertensive agents, highlighting the need to consider hypercortisolism in those with rHTN, irrespective of their T2D status.^15^ Indeed, a 2012 study from Brazil found that 1 in 4 individuals with rHTN may have endogenous hypercortisolism.^22^ Here, we describe the rationale and design of the first large, observational, multicenter study assessing the prevalence of endogenous hypercortisolism in a population with rHTN (MOMENTUM; NCT06829537).

## Materials and methods

### Study design and participants

MOMENTUM is an observational, noninterventional, multicenter study assessing the prevalence of endogenous hypercortisolism in approximately 1,000 individuals with rHTN (Central Illustration). Resistant hypertension is defined according to the 2017 AHA criteria,^2^^,^^3^ which were the U.S. guidelines available at the time of study commencement, as: 1) SBP above target (≥130 mm Hg) despite the concurrent use of 3 or more antihypertensive medications from different classes at maximally tolerated doses, with 1 medication being a diuretic; or 2) SBP at any level requiring the concurrent use of 4 or more antihypertensive medications from different classes. Clinically appropriate doses of antihypertensive medications are defined according to the investigator’s judgment and considered equivalent, for purposes of the study, to “maximally tolerated doses.” The study is being conducted at approximately 52 sites across the United States, reflecting a range of clinical practice settings and specialties, including academic, private practice, and research centers, with principal investigators drawn from cardiology, nephrology, primary care, and endocrinology (Figure 1). The study is funded by Corcept Therapeutics Incorporated, Redwood City, California.

**Central Illustration fig3:**
[figure not shown]
**The MOMENTUM Study** ACTH = adrenocorticotropic hormone; CT= computed tomography; DST = dexamethasone suppression test.

**Figure 1 fig1:**
[figure not shown]
**MOMENTUM Study Sites^a^** The study is being conducted at approximately 52 sites reflecting a range of clinical practice settings and specialties. ^a^Multiple study sites in the same city are represented by separate pins.

### Eligibility criteria

MOMENTUM is enrolling adults aged ≥18 years with rHTN. Exclusion criteria include factors that may result in an incorrect rHTN diagnosis and common causes of difficult-to-interpret (or “false-positive”) DST results. These include.•Investigator-determined white coat hypertension or nonadherence to blood pressure medications•Systemic glucocorticoid exposure ≤3 months before screening•Estimated glomerular filtration rate of <30 mL/min/1.73 m^2^•Severe acute psychiatric, medical, or surgical illness•Excessive alcohol consumption•Pregnancy or lactation•Use of oral contraceptives•Severe untreated sleep apnea

A complete list of exclusion criteria is shown in Table 1.

**Table 1 tbl1:** MOMENTUM Study Inclusion and Exclusion Criteria

Inclusion criteria	• Aged ≥18 years • Resistant hypertension, defined according to AHA criteria (SBP ≥130 mm Hg despite the use of ≥3 antihypertensive medications of different classes, including a diuretic, at maximally tolerated doses or requiring ≥4 medications from different classes regardless of SBP)
Exclusion criteria	• Investigator-determined white coat hypertension (ie, elevated blood pressure in the office only) • Investigator-determined nonadherence to blood pressure medications • Systemic glucocorticoid medications exposure (excluding inhalers or topical) ≤3 months of screening • Historical eGFR <30 mL/min/1.73 m^2^ • Investigator-determined: ◦ Severe untreated sleep apnea ◦ Excessive alcohol consumption (eg, >14 units/week for male, >7 U/week for female) ◦ Severe acute psychiatric, medical, or surgical illness • Pregnant or lactating • History of congenital adrenal hyperplasia • Diagnosed with endogenous hypercortisolism and/or has used or plans to use endogenous hypercortisolism medications^a^ • History of hypersensitivity or severe reaction to dexamethasone • Individuals on OCPs who are unable to stop for ≥6 weeks prior to screening

AHA = American Heart Association; eGFR = estimated glomerular filtration rate; OCP = oral contraceptive pills; SBP = systolic blood pressure.

a Mifepristone, metyrapone, osilodrostat, ketoconazole, fluconazole, aminoglutethimide, etomidate, octreotide, lanreotide, pasireotide, or long-acting octreotide or pasireotide.

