### Outcomes

The study’s primary endpoint is the prevalence of endogenous hypercortisolism in a population with rHTN. Endogenous hypercortisolism is defined as a cortisol level of >1.8 μg/dL after a 1-mg overnight DST with adequate concomitant dexamethasone levels (≥140 ng/dL). The dexamethasone level cutoff of 140 ng/dL, rather than the Endocrine Society–recommended cutoff of 220 ng/dL,^13^ is based on the normal range of the assay used in the central laboratory for the study (ARUP Laboratories). Dexamethasone is measured by a validated liquid chromatography with tandem mass spectrometry method with assay validation according to Clinical and Laboratory Standards Institute guidance under College of American Pathologists/Clinical Laboratory Improvement Amendments regulations. The threshold of 140 ng/dL corresponds to the lower reference limit of dexamethasone observed in the control population used to validate the assay and is concordant with reference intervals reported by other clinical reference laboratories. For participants with dexamethasone levels <140 ng/dL, the DST can be repeated using a 4-mg dose. If the dexamethasone level does not reach ≥140 ng/dL after repeat testing, the test is considered invalid, and the data are not included in the primary endpoint analysis.

Secondary endpoints include assessment of clinical and laboratory characteristics associated with an increased likelihood of endogenous hypercortisolism, proportion of individuals with markers of hyperaldosteronism and other causes of hypertension, and proportion of individuals with endogenous hypercortisolism and rHTN who have abnormal adrenal imaging. Exploratory endpoints include assessment of the proportion of participants with post-DST cortisol levels of 1.2 to 1.8 μg/dL and those with levels <1.2 μg/dL and their associated clinical and laboratory characteristics.

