Visit 2: fasting; 8 AM (dexamethasone taken prior evening)	
Pituitary/adrenal hormone levels	Serum cortisol, reflex dexamethasone levels for participants with post-DST cortisol >1.8 μg/dL, plasma ACTH
Glucose levels	Serum glucose
Lipid metabolism	Total cholesterol, low-density lipoprotein-cholesterol, high-density lipoprotein-cholesterol, very low-density lipoprotein-cholesterol, triglycerides
Visit 3: 8 AM (for subjects with post-DST cortisol >1.8 ug/dL)	
Pituitary/adrenal hormone levels	Plasma ACTH, serum cortisol

ACTH = adrenocorticotropic hormone; ALT = alanine aminotransferase; APRI = aspartate aminotransferase-to-platelet-ratio index; AST = aspartate aminotransferase; DHEAS = dehydroepiandrosterone sulfate; DST = dexamethasone suppression test; eGFR = estimated glomerular filtration; FIB-4 = fibrosis-4; HbA1c = hemoglobin A1c; NT-proBNP = N-terminal-pro-brain natriuretic peptide; UACR = urine albumin-to-creatinine ratio.

a Percent and absolute.

Participants with a post-DST cortisol level of ≤1.8 μg/dL are informed of their normal cortisol level, and no additional visits are required. Participants with a post-DST cortisol level of >1.8 μg/dL attend visit 3 within 2 weeks of the receipt of the DST result. Visit 3 entails a nonfasted morning blood draw to test ACTH and cortisol levels and scheduling of a noncontrast adrenal computed tomography scan. The total study duration is anticipated to be <4 weeks for most participants. Further clinical workup for participants with post-DST cortisol >1.8 μg/dL and potential treatment of the hypercortisolism is not mandated within the study. Rather, it will follow the local standard of care at each participating site.

Safety data (ie, adverse events, laboratory test results, and physical findings) are collected throughout the study, and patients are monitored on an ongoing basis. As this is a noninterventional study, an adverse event is defined as any unfavorable or unintended event related to a study procedure, such as a blood draw or imaging procedure, that occurs during the study.

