### Study limitations

Limitations of the study include that rHTN was determined based on a one-time in-office blood pressure measurement and investigator judgment as to participant adherence with at-home blood pressure checks and blood pressure medications. To address this limitation, in-office blood pressure was assessed in a consistent manner using the same in-office automated blood pressure device. Blood pressure was measured 3 times automatically, with a 1-minute interval between each measurement, without the investigator present. The mean blood pressure was used to determine eligibility. Out-of-office blood pressure measurements were reviewed with each participant to support the investigator in ensuring participants met the eligibility criteria. Similarly, adherence to blood pressure medications was based on participant interviews and investigator judgment. To minimize confounding of the DST results, the inclusion and exclusion criteria were carefully designed to rule out the most common confounding factors, including exogenous glucocorticoid exposure, oral contraceptive use, and specific comorbidities. Attainment of adequate dexamethasone levels was also ensured.

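### Eligibility treats oral contraceptives, but no other oral oestrogen, as a confounder of the DST, so users of other products can be counted as cases

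*Protocol article*

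**What the plan says.** The Eligibility criteria section of the protocol article explains that the exclusions are aimed partly at "common causes of difficult-to-interpret (or “false-positive”) DST results", and its summary list includes oral contraceptive use. It then states: "A complete list of exclusion criteria is shown in Table 1".

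The only drug entry in Table 1 that bears on oestrogen is "Individuals on OCPs who are unable to stop for ≥6 weeks prior to screening", and the table footnote defines the term: "OCP = oral contraceptive pills". Menopausal hormone therapy and other oral oestrogen appear nowhere in the article.

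The Outcomes section fixes the case definition: "Endogenous hypercortisolism is defined as a cortisol level of >1.8 μg/dL after a 1-mg overnight DST", subject to a dexamethasone level of at least 140 ng/dL. Table 2 lists the hormone tests at visit 2: "Serum cortisol, reflex dexamethasone levels for participants with post-DST cortisol >1.8 μg/dL, plasma ACTH". Neither corticosteroid-binding globulin nor free cortisol is listed. Under Statistical methods, every eligible enrolled participant with a valid DST enters the primary analysis.

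Study limitations says that the criteria were designed to "rule out the most common confounding factors, including exogenous glucocorticoid exposure, oral contraceptive use, and specific comorbidities".

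**The concern.** The study accepts that oral contraceptives can make a DST hard to interpret and takes steps to remove them. If the reason is that oral oestrogen raises the binding protein, and so the total cortisol that the endpoint thresholds, the same reason applies to oral oestrogen taken for other purposes. The article does not state this mechanism. It is general pharmacology, and I use it as an assumption.

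If it holds, a false-positive source of the kind the exclusions target stays in the cohort. The error goes one way, so it raises the estimated prevalence, and the confidence interval does not reflect it. It can also reach other planned analyses:

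- the logistic models of factors associated with hypercortisolism, where oestrogen use, or characteristics that go with it, could appear as associated factors;
- the proportion of cases with abnormal adrenal imaging, whose denominator would contain false cases.

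**Working it through.** **Step 1: follow one participant through the plan.** Take a postmenopausal woman with resistant hypertension who uses an oral oestrogen product that is not a contraceptive, and suppose that her post-DST cortisol is 2.3 μg/dL.

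- Table 1: no criterion excludes her on account of the product.
- Dexamethasone check: this verifies that enough dexamethasone was present. Hers is adequate, so the test is valid. The check says nothing about binding protein.
- Visit 2 tests: nothing listed separates raised total cortisol from raised free cortisol.
- Case definition: 2.3 exceeds 1.8, so she is a case.
- Visit 3: ACTH, cortisol and adrenal imaging follow, but the case definition does not use them to reclassify anyone.
- Primary analysis: she is eligible with a valid DST, so she is counted.

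**Step 2: the plan's own precision.** Statistical methods gives about 1,000 participants and an expected prevalence of 10 to 25%, with no target interval width, so the sample size cannot be reproduced. The implied 95% half-width is 1.96 × √(p(1 − p)/n):

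- p = 10%: 1.96 × √(0.10 × 0.90/1000) = 1.86 points (Wilson interval 8.29 to 12.02%)
- p = 25%: 1.96 × √(0.25 × 0.75/1000) = 2.68 points (Wilson interval 22.42 to 27.78%)

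**Step 3: illustrative bias.** Let f be the share of all participants on other oral oestrogen, FP the false-positive rate among exposed participants without the disease, and p the true prevalence, taken as the same in exposed and unexposed. Then

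bias = f × (1 − p) × FP.

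Neither f nor FP is in the article. I assume f = 0.5 to 5% and FP = 10 to 50%.

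| p | f | FP | Calculation | Bias (points) | False positives per 1,000 | Bias ÷ half-width |
|---|---|---|---|---|---|---|
| 10% | 0.5% | 10% | 0.005 × 0.90 × 0.10 | 0.05 | 0.5 | 0.02 |
| 10% | 2% | 25% | 0.02 × 0.90 × 0.25 | 0.45 | 4.5 | 0.24 |
| 10% | 5% | 50% | 0.05 × 0.90 × 0.50 | 2.25 | 22.5 | 1.21 |
| 25% | 0.5% | 10% | 0.005 × 0.75 × 0.10 | 0.04 | 0.4 | 0.01 |
| 25% | 2% | 25% | 0.02 × 0.75 × 0.25 | 0.38 | 3.8 | 0.14 |
| 25% | 5% | 50% | 0.05 × 0.75 × 0.50 | 1.88 | 18.8 | 0.70 |

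**Step 4: reading.** Only the most extreme combination at p = 10% exceeds the half-width. In the middle case the bias is about a quarter of it or less. Sampling error shrinks as n grows, but n does not appear in the bias formula.

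**The case against.** The case against giving this weight has several parts.

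- **The mechanism is not in the article.** It mentions neither oestrogen nor binding globulin. This stands, and the point depends on a labelled assumption.
- **The limitations text does not claim complete control.** A reader might infer that the study says it has ruled out oestrogen. It does not: it speaks of the most common confounders and names oral contraceptive use. There is no contradiction, only wording from which oestrogen could be taken as dealt with.
- **How common the exposure is cannot be known.** It is tempting to say that menopausal oestrogen is likelier than contraceptive use in this population. The article gives no sex mix, age distribution or hormone use, so it does not support that.
- **A distorted sex comparison is not shown.** Sex is not among the preplanned subgroups, which are cardiac or carotid, cardiovascular, renal and glycaemic. Demographics are summarised by hypercortisolism status, and the covariates of the logistic models are not listed.
- **The analysis plan is not shown and may contain a sensitivity analysis.** It may, and its absence from the article is not the criticism. The criticism concerns the stated eligibility and case definition, which such an analysis would supplement but not change. Because Table 1 is declared complete, condensation by the article does not explain the gap.
- **Changing eligibility during enrolment would be untidy.** Agreed: it would create two eligibility regimes, and it is not needed.

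**Conclusion.** The point holds in a limited form. As written, the plan can count users of non-contraceptive oral oestrogen as having endogenous hypercortisolism, and no listed step would detect it. The bias in the primary prevalence is upward if the pharmacological assumption is right.

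Its size is unknown. The illustrative range of about 0.04 to 2.25 points rests entirely on assumed exposure and false-positive rates, and it is usually smaller than the sampling half-width of 1.9 to 2.7 points. A reader might infer a large distortion of the headline figure, but nothing in the article supports that. What justifies acting is that the bias runs in one direction, is not reduced by sample size, and can be examined cheaply with data already being collected.

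**What to change.** Leave Table 1 as it is, and handle the matter in the analysis and the reporting.

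1. From the medication history taken at visit 1, flag current or recent use of any oral oestrogen-containing product, with the same window of at least 6 weeks before screening that Table 1 applies to oral contraceptives. Flagging current users alone would leave recent users unmarked.
2. Before the analysis plan is signed off, prespecify the primary prevalence with its 95% CI, and the models of factors associated with hypercortisolism, with and without flagged participants. If the plan already does this, only item 3 remains.
3. Reword Study limitations to say that, among oral oestrogen exposures, eligibility excluded only oral contraceptives.

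The cost is one coded flag, one extra analysis row and a few participants fewer in the restricted estimate. There is no new procedure and no change to anyone's treatment. The recent-use part of the flag depends on the medication history recording when a product was stopped, which should be confirmed.

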### Outcomes

The study’s primary endpoint is the prevalence of endogenous hypercortisolism in a population with rHTN. Endogenous hypercortisolism is defined as a cortisol level of >1.8 μg/dL after a 1-mg overnight DST with adequate concomitant dexamethasone levels (≥140 ng/dL). The dexamethasone level cutoff of 140 ng/dL, rather than the Endocrine Society–recommended cutoff of 220 ng/dL,^13^ is based on the normal range of the assay used in the central laboratory for the study (ARUP Laboratories). Dexamethasone is measured by a validated liquid chromatography with tandem mass spectrometry method with assay validation according to Clinical and Laboratory Standards Institute guidance under College of American Pathologists/Clinical Laboratory Improvement Amendments regulations. The threshold of 140 ng/dL corresponds to the lower reference limit of dexamethasone observed in the control population used to validate the assay and is concordant with reference intervals reported by other clinical reference laboratories. For participants with dexamethasone levels <140 ng/dL, the DST can be repeated using a 4-mg dose. If the dexamethasone level does not reach ≥140 ng/dL after repeat testing, the test is considered invalid, and the data are not included in the primary endpoint analysis.

Secondary endpoints include assessment of clinical and laboratory characteristics associated with an increased likelihood of endogenous hypercortisolism, proportion of individuals with markers of hyperaldosteronism and other causes of hypertension, and proportion of individuals with endogenous hypercortisolism and rHTN who have abnormal adrenal imaging. Exploratory endpoints include assessment of the proportion of participants with post-DST cortisol levels of 1.2 to 1.8 μg/dL and those with levels <1.2 μg/dL and their associated clinical and laboratory characteristics.

The study is also evaluating whether the degree of cortisol elevation post-DST is predictive of comorbidity severity or the presence and size of adrenal nodules. Several subgroup analyses are preplanned; patient demographics, clinical characteristics, blood pressure, medical history, and select medication use will be summarized overall and by endogenous hypercortisolism status within key subgroups. The subgroups will be defined by cardiac/carotid artery disorders (stratified by atrial fibrillation, heart failure, coronary artery disease, and other cardiac disorders), patients without cardiac or carotid artery disorders, broader cardiovascular disease status, renal function (estimated glomerular filtration rate ≥60, 45-59, and <45 mL/min/1.73 m^2^ using combined creatinine-cystatin C), and glycemic control (hemoglobin A1c categories ≥7.5%, ≥6.5%, 5.7%–<6.5%, and <5.7%). Simple and multiple logistic regression models will be used to evaluate factors associated with differences between groups.

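### The primary endpoint accepts positives at dexamethasone ≥140 ng/dL instead of the cited 220 ng/dL; this can only raise the prevalence or leave it unchanged, and the article describes no result at 220

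*Protocol article*

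**What the plan says.** All references are to the protocol article.

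- **Case definition (Outcomes).** The primary endpoint is the prevalence of endogenous hypercortisolism. A case needs cortisol above 1.8 μg/dL and a dexamethasone level of at least 140 ng/dL.
- **Departure from the guideline (Outcomes).** The article states its choice openly: "The dexamethasone level cutoff of 140 ng/dL, rather than the Endocrine Society–recommended cutoff of 220 ng/dL".
- **Reasons given (Outcomes).** The cutoff "is based on the normal range of the assay used in the central laboratory for the study". The level is measured by a validated LC-MS/MS method. The value "corresponds to the lower reference limit of dexamethasone observed in the control population used to validate the assay", and it "is concordant with reference intervals reported by other clinical reference laboratories".
- **Who is measured (Table 2, Visit 2).** The listed test is "reflex dexamethasone levels for participants with post-DST cortisol >1.8 μg/dL".
- **Below the cutoff (Outcomes).** A participant under 140 ng/dL can have the test repeated. If the level is still under 140, the test is invalid and leaves the primary analysis.
- **Analysis (Statistical methods).** Eligible participants with a valid test contribute to a proportion with a 95% CI. The planned size is about 1,000, with prevalence expected between 10% and 25%.
- **Limitations (Study limitations).** "Attainment of adequate dexamethasone levels was also ensured".
- **SAP (Ethics and data sharing).** A separate SAP is to be signed off before data analysis. It is not available here.

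**The concern.** The dexamethasone check exists so that a failure to suppress cortisol is not read as disease when too little drug was present. The question for any cutoff is therefore whether that level suffices to suppress cortisol. The reasons in Outcomes answer different questions. Assay validation shows that the level is measured well, and a lower reference limit shows what levels the controls reached. Agreement with other laboratories shows that those levels are usual. None of the three shows sufficiency at 140 ng/dL, and the article gives no suppression data at that level.

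A positive participant with dexamethasone between 140 and 219 ng/dL is a case here and would not meet the cutoff the article itself cites. How much of the reported prevalence comes from such participants will not be visible unless it is reported. The planned 95% CI covers sampling error only; it does not reflect the choice of cutoff, and a larger sample would not reduce its effect. The Discussion says that differing tests and definitions limited comparability among earlier studies, and the Conclusions hope to inform guidelines. Showing how far the headline figure depends on this cutoff would serve both aims.

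**Working it through.** **Plan's own figure.** Statistical methods states no target precision or CI width for about 1,000 participants, so there is no figure to reproduce.

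**Inputs from the article.** Cutoff used 140 ng/dL; cutoff cited 220 ng/dL; n about 1,000, taken here as 1,000 valid tests; expected prevalence 10% to 25%; tests that stay below the cutoff are excluded.

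**Inputs assumed.** Observed prevalence p = 20%, so x = 200 positives. The share f of positives at 140–219 ng/dL is not in the article; 5%, 10% and 15% are used for illustration.

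**Step 1: direction.** Dexamethasone is listed only when cortisol exceeds 1.8 μg/dL, so the adequacy rule can remove positives and never negatives. Let k = f·x. Removing k positives changes x/n to (x − k)/(n − k), which is no larger than x/n. With other results fixed, moving from 220 down to 140 can only raise the estimate or leave it unchanged.

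**Step 2: sampling error.** Half-width = 1.96 × √(p(1 − p)/n) = 1.96 × √(0.2 × 0.8/1000) = 2.48 points. The same formula gives 1.86 points at 10% and 2.68 points at 25%.

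**Step 3: size under the assumed shares, p = 20%.**

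| f | k | Dropped as invalid, (x − k)/(n − k) | Shift | All counted negative, (x − k)/n |
|---|---|---|---|---|
| 5% | 10 | 190/990 = 19.2% | 0.8 | 19.0% |
| 10% | 20 | 180/980 = 18.4% | 1.6 | 18.0% |
| 15% | 30 | 170/970 = 17.5% | 2.5 | 17.0% |

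At the ends of the expected range, dropping 5%, 10% and 15% of positives gives 9.55%, 9.09% and 8.63% in place of 10%, and 24.05%, 23.08% and 22.08% in place of 25%.

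**Step 4: when the shift matches sampling error.** The shift is p·f(1 − p)/(1 − p·f). Setting it equal to the half-width gives f of about 20% at p = 10%, 15% at p = 20% and 14% at p = 25%. For smaller shares the shift is less than the half-width.

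**Step 5: what a result at 220 would mean.** Participants at 140–219 ng/dL are not offered the repeat test, because the trigger is a level under 140. Had they been retested under a 220 rule, with m confirmed positive and r negative, the prevalence would be (x − k + m)/(n − k + m + r). Since m cannot exceed k, this never exceeds x/n. It normally lies above the dropped-as-invalid figure and falls below it only if few retests are positive. With k = 20 and every retest resolved, 4 positives give 184/1000 = 18.40%, just above 180/980 = 18.37%, and 3 give 183/1000 = 18.30%, just below. The strict floor is the all-negative column.

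**The case against.** The strongest reply is that this is a disclosed and reasoned choice, not an error. Outcomes names the guideline value, states the departure and gives assay-based reasons, and the definition is the same in the Abstract, Outcomes and Figure 2. That stands: there is no contradiction to report.

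Four stronger readings are tempting, and the article does not support them.

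- **That no analysis at 220 is planned.** The article describes none, but a sensitivity analysis of this kind commonly sits in the SAP, which is not shown.
- **That positives at 140–219 are under-dosed and the prevalence is inflated.** This takes 220 as right for this assay. The article argues that its cutoff is assay-specific, and neither value can be judged from the article. What can be said is that sufficiency at 140 is not shown.
- **That comparison with other studies is impossible.** The article gives no dexamethasone cutoff for the earlier US study in type 2 diabetes or for the Brazilian study in resistant hypertension, so nothing shows that they used 220.
- **That the sentence in Study limitations is wrong.** It uses the term adequate as Outcomes defines it, at 140 or above. Its wording alone is not a finding.

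Two further objections also stand. The shares of 5% to 15% are assumed, and at 5% and 10% the shift is smaller than sampling error. A later cut at 220 also removes people whom a 220-based study could have retested, so it does not reproduce a guideline-based prevalence.

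None of this alters the direction of the effect. The cutoff is fixed in the article as part of the primary endpoint, and the stated reasons do not address sufficiency for suppression.

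**Conclusion.** The point holds as a modest improvement and not as an error. The primary endpoint accepts positives at a dexamethasone level below the guideline value the article cites, on grounds that do not show the level is enough to suppress cortisol. With other results fixed, the choice can only raise the prevalence or leave it unchanged. That direction rests on Table 2, where dexamethasone is a reflex test for cortisol above 1.8 μg/dL.

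The amount is unknown. If 5% to 15% of 200 positives in 1,000 valid tests lay at 140–219 ng/dL and were dropped, the prevalence would be 19.2% to 17.5% instead of 20.0%. Only the top of that assumed range matches the ±2.5-point half-width. Whether the SAP already contains a result at 220 cannot be known from the article. No judgement is made on which cutoff is clinically right.

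**What to change.** Keep 140 ng/dL as the primary definition. Before the SAP is signed off, specify the following, or confirm that it is already there:

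1. the number of positives with dexamethasone at 140–219 ng/dL;
2. a sensitivity analysis giving the prevalence and 95% CI with those positives treated as invalid, shown beside the primary result.

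Label the second figure a lower bound and not a guideline-based prevalence, and say that participants at 140–219 were not offered the repeat test. The strict floor, with all of them counted as negative, follows from the same count and can go in a footnote.

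The levels are already collected in participants with cortisol above 1.8 μg/dL, so no new testing is needed. The cost is one extra analysis and a second figure that may be slightly lower than the first.
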